### Ethnicity

In industrialised societies, some minority ethnic groups are known to have a substantially elevated risk of T2DM. South Asians (SAs), the largest ethnic minority in the UK, have prevalence and progression rates for diabetes that are up to four times greater than the general population [27]. This elevated risk of chronic disease is compounded by lifestyle factors, of which the most notable is physical inactivity. SAs residing in the UK have been shown to be substantially less active with lower levels of cardiovascular fitness than the general population [28–30]. This differential in physical activity behaviour and levels of cardiorespiratory fitness has been linked to the increased prevalence of chronic disease and higher rates of insulin resistance seen in SA populations [30, 31]. Therefore SAs represent a priority group in the prevention of T2DM. However, there is limited evidence that diabetes prevention programmes within a European context have been effective at targeting lifestyle behaviours and improving health in minority ethnic groups.

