### Algorithm for inclusion for participants found to have normal glycaemia at baseline

All individuals found to have normal glycaemia at baseline are included in the study provided they meet the inclusion criteria requiring a historical blood glucose level within the prediabetes range within the previous 5 years.

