### Randomisation

Once baseline data have been collected, participants are randomised (stratified by sex and ethnicity) using an online randomisation tool hosted at the University of Leicester Clinical Trials Unit. Individuals are randomised (1:1:1) to the control group, the Walking Away Group or the Walking Away Plus Group. The exception to this is individuals recruited from the same household, who are randomised to the same group. Participants are informed of their allocated treatment after baseline measures are completed. Study allocation is concealed from the study measurement teams conducting the 12-month and 48-month follow-up.

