#### Secondary outcome

Given that around 95 % of the general population fail to meet the Chief Medical Officer’s physical activity guidelines when measured objectively by accelerometers [60], this study also allows for the 10 % difference in those meeting the current physical activity recommendation to be detected at follow-up based on 1-beta = 0.8, alpha = 0.025. Consistent with the calculation for ambulatory activity, this study has sufficient power (1-beta = 0.8, alpha = 0.025) to measure a 10 minute/day difference in change in the time spent in moderate-to-vigorous intensity physical activity based on previous work undertaken by our group [16].

This study has sufficient (1-beta = 0.8, alpha = 0.025) power to allow for clinically meaningful differences for change in the biochemical measures to be detected in the entire study cohort and after stratification by ethnicity; fasting glucose (0.3 mmol/l), 2-h glucose (1 mmol/l) and HbA_1c_ (0.25 %).

Furthermore assuming a conversion rate to T2DM in the control group of at least 24 % over the course of the entire study (4 years), we will have an 80 % power to detect a 40 % reduction in the relative risk of T2DM in both intervention groups compared to the control group. The estimated conversion rate is at the lower level reported for traditionally defined prediabetes [7, 61]. We anticipate that the inclusion of an HbA_1c_ defined prediabetes in this study will act to marginally lower the conversion rates, whilst the inclusion of a large South Asian group will act to increase the conversion rates.

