### Data analysis

Analysis will involve two *a priori* comparisons; both intervention groups will be compared to the control group. Should any of these comparisons reveal a significant difference, then a third *a priori* comparison will be undertaken by comparing the difference between intervention groups - this will be included as a secondary analysis. Multiple linear regression analysis will be used to investigate the differences in the change in physical activity level achieved between groups at 48 months, after adjusting for potential areas of bias between groups, valid accelerometer wear time and the number of valid wear days. Analysis will be conducted on the cohort as a whole and stratified by ethnic group; interaction terms will be used to quantify the effect of ethnic group. We will also use interaction terms to assess whether the effects of the interventions are modified of gender, age, ethnicity, family history of T2DM or whether prediabetes status was confirmed at baseline; significant interactions will followed by stratified analysis. We will also assess change in physical activity at 12 months as a secondary outcome. The primary analysis will be based on analysing those with complete data at each time point in the group to which they were randomised. A sensitivity analysis will be undertaken to assess the impact of imputing missing data through multiple imputation and through a per-protocol analysis by removing those that failed to attend the initial Walking Away session in both intervention groups; per-protocol analysis for the Walking Away Plus group will be defined as removing those that that failed to attend the initial Walking Away session OR those that failed to register for or actively stopped their text messaging support via the STOP function within the first 2 months.

Analysis of secondary biochemical and anthropometric outcomes will be analysed using the same strategy and at the same time-points as that described for the primary outcome. Differentials in the time to T2DM between groups will be plotted using the Kaplan–Meier method for comparing survival curves; the log rank test will be used to assess for differences between the groups.

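### The log-rank test for time to T2DM names no strata, although randomisation is stratified by sex and ethnicity: a small, avoidable loss of efficiency

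*Protocol article*

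**What the plan says.** The Data analysis section gives T2DM incidence its own method. The curves are to be plotted by Kaplan-Meier, and "the log rank test will be used to assess for differences between the groups". No stratum or covariate is mentioned. The adjusted linear regression in the same section is for physical activity, and it is carried over only to the biochemical and anthropometric secondary outcomes.

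Under Randomisation, "participants are randomised (stratified by sex and ethnicity) using an online randomisation tool", and "Individuals are randomised (1:1:1) to the control group, the Walking Away Group or the Walking Away Plus Group".

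On prognosis, the Ethnicity section of the Background reports that South Asians "have prevalence and progression rates for diabetes that are up to four times greater than the general population". The Secondary outcome part of Sample size expects the large South Asian group to raise the conversion rate in this trial. At least 25% of the cohort is to be South Asian (Study design).

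On power for this endpoint, the Secondary outcome part assumes a control conversion rate of at least 24% over four years and states that "we will have an 80 % power to detect a 40 % reduction in the relative risk of T2DM" in both intervention groups compared with control.

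On baseline glycaemia, "All individuals found to have normal glycaemia at baseline are included in the study", provided they have a qualifying earlier value. HbA1c is measured at baseline, 12 and 48 months (Table 4), and local diagnosis of T2DM is based on it (Biochemical variables).

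**The concern.** When randomisation balances a prognostic factor and the test ignores it, the arms differ by chance less than the test's variance formula supposes. The statistic is then too small on average under the null, so the true error rate falls below nominal and some power is given up. Ethnicity is such a factor here: the design balances it, and the protocol itself treats it as prognostic for conversion. The trial pays for stratification at randomisation and, as the sentence is written, does not use it for this endpoint.

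The sentence also names only a test. A log-rank test alone gives no effect size, and the analysis would naturally report one. Baseline HbA1c is the obvious covariate for that estimate, because it is the starting value of the variable on which T2DM is diagnosed.

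What is at stake is efficiency on one secondary outcome. Validity is not in question.

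**Working it through.** **Inputs from the protocol article.** 436 randomised per arm, 30% drop-out, alpha 0.025 per comparison (Sample size, Primary outcome); control 4-year risk 24% and a 40% relative reduction (Sample size, Secondary outcome); 25% South Asian (Sample size); 1:1 within each intervention-control comparison (Randomisation); South Asian progression up to fourfold (Ethnicity).

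**Assumptions.** Alpha is two-sided, and 0.025 and the 30% drop-out also apply to T2DM (the T2DM sentence gives neither). Hazards are constant. Sexes are split equally, with a sex hazard ratio of 1.3. Arms are exactly balanced within the four sex-by-ethnicity strata.

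**Step 1: evaluable number per arm.** From the primary outcome, n = 2(2.241 + 0.842)² × 4000² / 1000² ≈ 304.2, rounded up to 305. Then 305 / 0.70 = 435.7, rounded up to 436, which matches the protocol.

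**Step 2: reproduce the stated 80% for T2DM.** The intervention risk is 0.24 × 0.60 = 0.144.
- Two proportions: the mean risk is 0.192. Power = Φ[(0.096√305 − 2.241√(2 × 0.192 × 0.808)) / √(0.24 × 0.76 + 0.144 × 0.856)] = Φ(0.774) = 78.1%.
- Schoenfeld: HR = ln(0.856)/ln(0.76) = 0.567; events = 305 × (0.24 + 0.144) ≈ 117. Power = Φ[|ln 0.567| × √(117/4) − 2.241] ≈ Φ(0.83) = 79.8%.

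Both are within 2 points of 80% and use no stratification, so the stated figure is already that of the plain test. With alpha 0.05 the two formulas give 85.5% and 86.8%. With 436 per arm and alpha 0.025 they give 91.4% and 92.4%.

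**Step 3: plain against stratified log-rank, by simulation.** Exponential times were censored at 4 years, with overall risks held at 24% and 14.4%. There were 8,000 runs for power and 12,000 for type I error. The stratified test used sex by ethnicity.

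| Per arm | South Asian HR | Power, plain | Power, stratified | Type I, plain | Type I, stratified |
|---|---|---|---|---|---|
| 305 | 1 | 78.3% | 78.3% | 0.0229 | 0.0238 |
| 305 | 2 | 78.6% | 79.5% | 0.0228 | 0.0250 |
| 305 | 4 | 80.3% | 83.7% | 0.0169 | 0.0268 |
| 436 | 2 | 91.5% | 91.8% | 0.0258 | 0.0271 |
| 436 | 4 | 92.5% | 94.5% | 0.0183 | 0.0269 |

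At ratio 4 with 305 per arm and events placed at the 12- and 48-month visits, power is 80.1% plain and 83.4% stratified, and type I error is 0.0171 and 0.0254.

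The Monte Carlo standard error of a type I error near 0.025 is √(0.025 × 0.975 / 12,000) ≈ 0.0014. The plain test is therefore clearly conservative at ratio 4 but not distinguishable from nominal at ratio 2. A separate simulation at ratio 4, stratifying by ethnicity alone, gave 80.1% against 83.8% power and type I error of 0.017 against 0.025.

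**Step 4: baseline HbA1c, illustration only.** The protocol gives no conversion rate by HbA1c level. A normally distributed covariate with an assumed log-hazard SD of 0.9 was used as a stand-in (305 per arm, 5,000 runs).

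| South Asian HR | Plain | Sex and ethnicity strata | Plus covariate quartiles |
|---|---|---|---|
| 2 | 79.1% | 79.9% | 83.8% |
| 4 | 80.0% | 82.5% | 87.9% |

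The last column rests on the assumed SD. It cannot be claimed for this trial.

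**The case against.** The strongest reply is that this is a condensed article. Whether a secondary log-rank test is stratified, and which covariates enter a supporting model, is commonly settled in the analysis plan, and the text does not say that the test is unstratified. That has weight, and it keeps the point small. It does not remove it: the article gives T2DM a separate, named method, and as written that method is a plain test. If the analysis plan already stratifies, adding one word to the article closes the point.

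The second reply is that fourfold is a ceiling against the general population. It is not a hazard ratio among people already selected for prediabetes. That stands. The ratio within the trial may be much lower, and at 2 the difference is about 1 point.

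Four stronger readings are tempting, and the documents do not support them.
- *That the protocol reports different progression by sex or by HbA1c level.* It does so for ethnicity only. Its remark that HbA1c-defined prediabetes will slightly lower conversion concerns the route of entry and says nothing of risk by HbA1c level.
- *That the stated power is missed.* The 80% reproduces without stratification, and the plain test gives 78% to 80% in simulation at 305 per arm.
- *That a chance imbalance in baseline HbA1c would bias the comparison.* It is ordinary sampling variation, which the test already allows for; adjustment gains precision.
- *That the economic evaluation is affected.* The Health economics section builds its own survival model from control-arm progression and the effect of physical activity. It does not use the log-rank result.

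**Conclusion.** The point holds as a minor efficiency improvement. The planned test is valid and gives about the power claimed, but it leaves the randomisation factors unused for an endpoint on which the protocol expects ethnicity to matter. With 305 evaluable per arm and two-sided alpha 0.025, the power forgone is nil if ethnicity is not prognostic, about 1 point at a South Asian hazard ratio of 2 (type I error about 0.023), and about 3.5 points at 4 (type I error about 0.017).

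These figures assume constant hazards, 25% South Asian participants, balance within strata, and the primary outcome's alpha and drop-out applied to T2DM. The ratio of 2 is an assumption, and 4 is the protocol's own upper limit for a different comparison population. No gain from baseline HbA1c is included, because its size cannot be taken from the document.

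**What to change.** In Data analysis, replace the log-rank clause with wording to this effect: each intervention group will be compared with control by a log-rank test stratified by sex and ethnicity; the effect will be estimated from a time-to-event model with the same strata and continuous baseline HbA1c as a covariate; Kaplan-Meier curves and the unadjusted 48-month risk difference will be shown alongside. If a discrete-time or interval-censored model is chosen because conversion is assessed at the study visits, it should carry the same three terms.

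The cost is a sentence or two. Sex and ethnicity are recorded for randomisation, and baseline HbA1c is collected at both centres. Four strata are not too many: with 25% South Asian participants and an equal sex split, the smallest hold about 305 × 0.125 ≈ 38 per arm. The one drawback is that the hazard ratio becomes conditional on the strata and baseline HbA1c, while the protocol states its target as an overall relative reduction in risk. That is why the unadjusted risk difference belongs beside it.

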### Health economics

We will undertake a costing exercise to determine the cost of delivering the initial interventions covering expenditure such as educator time, educator training and quality assurance. In addition we will determine the cost of the follow-up maintenance support group-sessions and the staff and other costs of the individually tailored telephone and text messaging package for maintenance support. Resource use incurred will be costed using actual costs in the trial and/or standard references for unit costs such as Unit Costs of Health and Social Care [62]. In addition to the primary endpoint, we will analyse the within-trial impact of the interventions during the trial on other outcomes that are pertinent to the long-term economic analysis, i.e. use of antihypertensives and lipid-lowering therapies, blood pressure, health utility and incidence of T2DM.

Long-term costs and benefits of the interventions will be evaluated through a combination of the within-trial outcomes and decision-analytic modelling to simulate long-term incidence ofT2DM, microvascular complications arising from T2DM and cardiovascular events. Specifically for progression to T2DM, estimating long-term progression will require a statistical model built partly from incidence data from the trial. The underlying incidence curve will be based on rates of progression in the control arm, and a survival model with time-varying hazards will be built to demonstrate the effect of a unit change in physical activity on risk of T2DM over time. This will allow the impact of alternative assumptions about the degree of maintenance of physical activity beyond the 4-year follow-up period to be modelled. The underlying progression of T2DM beyond the 4-year follow-up will be estimated by the above 4-year survival curve and assumptions about medium-term maintenance of physical activity, but also informed by the trajectory of survival curves from long-term diabetes prevention studies such as the Finnish Diabetes Prevention study [63].

An important input for the modelling will be the effect of increasing physical activity on cardiovascular risk. The relationship between changes in physical activity and cardiovascular risk will be incorporated into an existing decision-analytic model of prevention of diabetes. This relationship will be informed by a recent study that specifically calculated the effect of change in ambulatory activity (steps per day) on cardiovascular disease risk [13]. The model will be chosen from existing models used previously for work for NICE [64] on prevention of diabetes or developed as part of the School for Public Health diabetes prevention theme within ScHARR, funded by the National Institute for Health Research (NIHR). The economic model aggregates the costs of the intervention, prescribed medications, therapy, the costs of one-off treatments (e.g. cost of amputation), and on-going treatment of complications (e.g. treatment following stroke). The cardiovascular risks of participants with prediabetes, or with diabetes will be estimated using the UKPDS risk engines [65, 66]. A further adjustment will be made so that the risk can be adapted for the South Asian population using evidence advised by clinical colleagues.

Separate evaluations will be undertaken for the overall group and for the South Asian subgroup. Cost-effectiveness will be reported in terms of incremental costs and QALYS and the incremental cost-effectiveness ratio. Uncertainty around the results will be explored through probabilistic sensitivity analysis and related techniques for identifying the most important drivers of uncertainty, which will be presented on a cost-effectiveness acceptability curve and a cost-effectiveness plane.

### Trial Steering Committee (TSC) and Data Monitoring and Ethics Committee (DMEC)

The trial is overseen by TSC comprising an independent chair, independent clinical and academic members and the principal investigator. This committee is responsible for the overall management and oversight of the trial. The steering committee are blinded to all information regarding treatment assignments until after the database is locked for final analysis.

A fully independent DMEC reports to the TSC. This comprises an independent chair and a statistician. The DMEC are responsible for the interests of participant safety and data integrity. The DMEC will undertake safety data reviews every nine months, unless otherwise deemed necessary. In addition the DMEC will also review analysis plans.

## Discussion

This trial will provide important insight regarding the long term effectiveness and cost-effectiveness of a group-based structured education programme for physical activity targeting those with prediabetes within primary care, and the effectiveness of a highly-tailored and evidence-based text-messaging and telephone follow-on system designed to support ongoing behaviour change and pedometer use. NICE guidelines on diabetes prevention recommend the use of group-based lifestyle intervention for prediabetes as the cornerstone of any diabetes prevention pathway [6], so it is important to investigate the use of structured education within the prevention domain. It is imperative that any intervention programme is carefully evaluated for both clinical and cost-effectiveness, as well as its capacity to be easily implemented into primary care. Whilst both the effectiveness and cost-effectiveness of structured education for those diagnosed with T2DM have already been established [34, 35], and is recommended by NICE as best clinical practice for the management of T2DM [33], there is a lack of translational research within the context of diabetes prevention. Consequently this limits the capacity of commissioners and policy makers to make informed evidence-based decisions regarding the implementation of national diabetes prevention programmes within primary care. Furthermore there is a need to establish what the optimal levels of ongoing support are to ensure any behaviour change is maintained, taking into account the limited resources available in most healthcare settings. This study evaluates highly-tailored, evidence-based text-messaging tool which requires few resources and time, and thus will help address both of these limitations.

The Walking Away from Diabetes structured educational programme and the follow-on text-messaging and telephone support system have been specifically designed to be translated into primary care. This type of lifestyle intervention in prediabetes could be easily added to other programmes currently on offer for the management of type 2 diabetes, thereby allowing a range of structured education packages and evidence-based mHealth interventions to be offered, to best serve the needs of the diabetes pathways within primary care.

## Trial status

Recruitment started in January 2014 and is still ongoing.

## Abbreviations

BIPQ: Brief illness perceptions questionnaire
DESMOND: Diabetes Education and Self-Management for Ongoing and Newly Diagnosed
DMEC: Data Monitoring and Ethics Committee
EPIC: European Prospective Investigation of Cancer and Nutrition
EQ-5D: European Quality of Life-5 Dimensions
HbA1c: Glycated haemoglobin
prediabetes: Impaired glucose regulation
NAVIGATOR: NateglinideAnd Valsartan in Impaired Glucose Tolerance Outcomes Research
NICE: National Institute of Health and Care Excellence
OGTT: Oral glucose tolerance test
PA: Physical activity
QALY: Quality adjusted life years
PREPARE: Prediabetes Risk Education and Physical Activity Recommendation and Education
PROPELS: The PRomotionOf Physical activity through structured Education with differing Levels of ongoing Support for those with prediabetes
SF-8: Short form 8
T2DM: Type 2 Diabetes Mellitus
TSC: Trial steering committee
WHO: World Health Organization
